# DRUG INFORMATION

## Psilocybin

### Pharmacology

Psilocybin is a natural product produced by numerous species of *Psilocybe* mushrooms. It is synthesized de novo and manufactured for clinical use to control potency and purity. The Controlled Substances Act currently classifies psilocybin as a Schedule I drug.

### Mechanism of Action

After absorption, psilocybin is enzymatically cleaved to produce psilocin, which acts as an agonist of serotonin receptors, including 5-HT2A. 5-HT2A receptor stimulation depolarizes layer 5 pyramidal neurons leading to an increased firing rate. This increased firing in prefrontal cortex results in increased glutamatergic recurrent network activity.

### Pharmacokinetics

Following oral administration (0.224 mg/kg) of psilocybin, average blood concentration of the active metabolite psilocin was calculated to be 8.2 ± 2.8 ng/mL after 105 ± 37 minutes, yielding an estimated dose-normalized bioavailability of psilocybin to be 52.7 ± 20% (N = 3). Psilocin typically appears in plasma within 15 minutes after oral administration. Psilocin half-life following oral administration of psilocybin was found to be approximately 3 ± 1.1 hours, and is detectable for up to 24 hours after administration. The levels of psilocin peaked at approximately 80 minutes; however, rates can vary between individuals.

Psilocin is metabolized to 4-hydroxyindole-3-acetic acid by deamination and demethylation via liver enzymes such as monoamine oxidase, and aldehyde. Psilocin is also extensively glucuronidated by the UDP-glucuronosyltransferase (UGT) family of enzymes, with the highest glucuronidation activity demonstrated by UGT1A10. The amount of psilocin glucuronide excreted renally has been shown to exceed that of psilocin over a 24-hr time period, and analysis of psilocin in urine over 24 hours after a single dose has shown that less than 4% of the overall clearance of psilocin occurs through renal excretion. The pharmacokinetics of psilocybin (as psilocin) are linear over the dose range of 0.3 – 0.6 mg/kg.

### Physical and Chemical Properties

Psilocybin is a tryptamine derivative presenting as a white crystalline solid with a melting point of 220-228°C. It is stable over extended periods in dark storage at controlled room temperature. Psilocybin is soluble in 20 parts boiling water or 120 parts boiling methanol.

[3-[2-(dimethylamino)ethyl]-1H-indol-4-yl] dihydrogen phosphate

[figure not shown]

**Figure 1.** Psilocybin molecular structure

Chemical Formula: C_12_H_17_N_2_O_4_P

Molecular Weight: 284.3

### Clinical Safety

The clinical safety of psilocybin has been extensively studied, both as a single agent and as adjunctive treatment in adult populations. Psilocybin is administered orally, and has been studied in open-label, and double-blind, controlled trials. Dosing regimens have ranged from 0.014 mg/kg to 0.6 mg/kg, administered as either a single dose, or multiple doses weeks apart.

The most common adverse experiences are psychological, including anxiety, and the induction of negative emotional states and paranoid/delusional thinking during psilocybin sessions. The most common physical adverse events are cardiovascular (increased blood pressure and heart rate), as well as nausea and headache.

A meta-analysis of eight double-blind, placebo-controlled studies including 110 healthy subjects who had received 1–4 oral doses of psilocybin (45–315 μg /kg body weight) showed that effects of psilocybin are dose-dependent, although other factors such as personality structure and the setting (e.g., environment) appear to modulate its overall effects. Although psilocybin dose-dependently induced profound changes in mood, perception, thought, and self-experience, most subjects described the experience as pleasurable, enriching, and non-threatening. Acute adverse drug reactions, characterized by strong dysphoria and/or anxiety/panic, occurred transiently only in the two highest dose conditions in a relatively small proportion of subjects (5 and 8% respectively). All acute adverse drug reactions were successfully managed by providing interpersonal support and did not require psychopharmacological intervention.

# STUDY DESIGN

## Description

Recruitment will target physicians or nurses with at least 1 month of frontline clinical experience during the COVID pandemic who meet DSM-5 criteria for a depressive disorder, including adjustment disorder with depressed mood.

Participants that meet eligibility criteria and have a screening MBI-HSS (MP) score that meets our working definition of burnout (emotional exhaustion subscale ≥ 27) and a ‘high’ score on one other subscale (either depersonalization ≥ 13 or personal accomplishment ≤ 21) as well as a PHQ-9 depression screen ≥ 10 will be offered enrollment and following a consenting process will be randomized to either MBSR or MBSR + PAP with 12 participants per group. PHQ-9 and MBI-HSS questionnaires may be administered prior to consenting to assess eligibility. Consenting will be completed in person with paper or electronic consenting forms. The MBSR group will complete an 8-week MBSR curriculum (online) through the University of Utah Resiliency Center led by [name], LCSW which includes a weekly 2.5-hour sessions over Zoom for 8 weeks and an 8 hour in-person retreat between weeks 6 and 7. If capacity within the University of Utah MBSR groups limits enrollment and feasibility we will incorporate the MBSR programs through Intermountain as well as Davis Behavioral Health. We will run subjects through the MBSR curriculum in flexible numbers concurrently until a total of 12 have completed this arm. The MBSR + PAP group will complete this same curriculum, however will substitute an 8-hour group-format psilocybin-assisted therapy session (with 25 mg psilocybin capsule) with 1:1 therapist to participant ratio instead of the MBSR retreat day. Each participant will have an assigned individual therapist present for the duration of the psilocybin dosing session. A lead therapist ([name] PhD) will also be present for all study sessions including the psilocybin dosing day and there will be at least one lead study monitor present for the duration of the psilocybin dosing day ([name] MD or [name] MD). The psilocybin intervention will be completed in groups of 2-6 individuals per cohort. Additionally, the MBSR + PAP group will have 3, 90-minute group preparatory sessions prior to the psilocybin session and 3 subsequent 90-minute integration sessions. The first integration session will occur 1-2 days following the psilocybin session. A communal music track will be played during the PAP session. After the enrollment and treatment of the first four patients, accrual will be placed on hold to ensure participant safety. If stopping rules are not met, we will continue with enrollment.

PAP Preparation sessions will focus on psychoeducation regarding the effects of psilocybin, guidance as to navigating the experience, establishing safety and trust with the therapist team, and specific mindfulness focused skills (drawing on the MBSR curriculum) that can be employed during the experience. The psilocybin session will employ a 1:1 therapist to participant ratio which is the same model as the HOPE trial run by this team. These sessions will also be video recorded with participant consent. This session will be conducted in a largely non-directive and supportive fashion similar to the current therapy model used in psychedelic-assisted therapy research. However, we will book-end the dosing day with specific mindfulness exercises drawing from the MBSR curriculum. At the end of this 8-hour session all participants will be assessed for safety to leave the premises including a screen for suicidality, a final set of vital signs and medical evaluation, as well as a cognitive assessment as to orientation. Rides and support person will be confirmed by the study team. The first integration session will occur within 48 hours of this dosing day however the therapist team will be available by phone throughout this time in case there is need for additional support. Subsequent integration sessions (2 additional) will be integrated into the MBSR curriculum, following the weekly group MBSR session. These sessions will focus on processing the experience and relevant emotional and psychological material as a group as well as integrating this with perspectives and insights gained through the mindfulness curriculum.

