# STUDY SUMMARY

| Title | PAPR: Psilocybin-assisted psychotherapy (PAP) + Mindfulness-based Stress Reduction (MBSR) for front-line healthcare provider COVID-related depression and burnout. |
| --- | --- |
| Short Title | PAPR |
| Protocol Identifiers (IRB – internal) |  |
| IND number | 163040 |
| Phase | Pilot |
| Design | Open-label, pilot trial. |
| Study Duration | 1.0 years |
| Study Center(s) | This is a single-center trial to be conducted at Huntsman Mental Health Institute |
| Objectives | **Primary Objectives**   - To assess the safety and tolerability of psilocybin in the study population. - To assess the feasibility to recruit, consent, and enroll healthcare providers in a study of psilocybin-assisted therapy + MBSR vs. MBSR and for those participants to remain in the study until completion. - To assess the effect that psilocybin-assisted therapy has on depression symptoms in healthcare providers with burnout as measured by the QIDS-SR-16.   **Secondary Objectives**   - To assess the changes in rates of provider burnout as measured by the Maslach Burnout Inventory for Medical Professionals (MBI-HSS (MP)) both in terms of rates of meeting criteria for burnout as well as mean reduction in score on the MBI. - To assess the long-term effect that psilocybin-assisted therapy and MBSR have on depression and anxiety symptoms in the study population. - To assess the effect psilocybin therapy and MBSR have on symptoms of post-traumatic stress syndrome. - To assess the effect psilocybin therapy and MBSR have on participant reported quality of life. - To assess the effect psilocybin therapy and MBSR have on participant reported feelings of connectedeness to self, other, and world.   **Exploratory Objectives**   - To assess the effect psilocybin therapy, in conjunction with an MBSR curriculum, has on state and trait mindfulness measures. - To assess participant-reported psilocybin experience on the day of medication administration and to assess the relationship between reported experience and depression and burnout response. - To use the Storyline Health AI platform to develop a model for precision research on psychedelic-assisted therapies and healthcare provider burnout and to better characterize predictors of response to mindfulness training and psilocybin therapy utilizing the Storyline Integrative Assessment tool. |
| Number of Subjects | 25 |

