| Diagnosis and Main Eligibility Criteria | **Key Inclusion Criteria:**   - Male or female healthcare providers aged ≥ 25 years old. - Participants must be physicians or nurses with at least 1 month of frontline clinical experience during the COVID-19 pandemic. - Screening MBI-HSS (MP) score that meets our working definition of burnout (emotional exhaustion subscale ≥ 27) and a ‘high’ score on one other subscale (either depersonalization ≥ 13 or personal accomplishment ≤ 21). - PHQ-9 depression screen ≥ 10. - Not taking regularly scheduled medications to treat depression and/or anxiety, including benzodiazepines, for at least 4 weeks prior to initiation of the study.   **Key Exclusion Criteria:**   - Prior systemic antidepressants, anti-psychotic, or anxiolytic medication within four weeks prior to psilocybin administration. - Personal history or immediate family members with schizophrenia, bipolar affective disorder, delusional disorder, schizoaffective disorder, psychosis, dementia, or other psychotic spectrum illness. - Currently meeting DSM-5 criteria for Dissociative Disorder, or other psychiatric conditions judged to be incompatible with the establishment of rapport or safe exposure to psilocybin. - Currently meeting DSM-5 criteria for Cluster B Personality Disorder). - Current or history within the last two years of meeting DSM-5 criteria of substance use disorder (excluding caffeine and nicotine). |
| Study Product, Dose, Route, Regimen | Psilocybin 25 mg PO |
| Duration of administration | One-time administration |
| Reference therapy | MBSR |
| Statistical Methodology | Feasibility will be assessed by the ability to recruit, consent, and enroll 24 patients in the trial, and for at least 16/24 patients to remain in the study until completion.  The key secondary analysis of QIDS-SR-16 and MBI-HSS(MP) will use mixed-effects models with fixed effects for time (enrollment, 2 weeks post psilocybin), and a random intercept term. The outcome variables are the estimated change from baseline to 2 weeks post psilocybin from these models. |

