# OBJECTIVES

## Primary Objectives

### Determine the acceptability, feasibility, and safety of psilocybin-assisted therapy (PAP) plus Mindfulness-Based Stress Reduction (MBSR) for front-line healthcare worker burnout.

*Primary Endpoint:* Acceptability of each modality will be determined by ease of enrollment and retention. Feasibility will be measured by the number of enrollees who successfully complete each modality in both study arms. Safety will be measured through the monitoring of adverse events (AEs) utilizing the CTCAE (NCI Common Terminology Criteria for Adverse Events Version 5.0), suicidal ideation utilizing the Columbia Suicide Severity Rating Scale (C-SSRS), administration of the Challenging Experiences Questionnaire (ChEQ), direct participant qualitative reports, and clinician observation.

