## Number of Patients

This study will enroll a total of 24 patients with 12 patients in each study arm.

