## Study Duration

Study therapy will be a total of 9 weeks duration (with 8-week MBSR curriculum) and patients will be followed for 6 months (180 days) after completion of the study intervention. There will be a total of two groups of 12 subjects per study arm. Total duration for the study will be approximately one year.

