## Randomization and study arm assignment

Participants who meet eligibility criteria and have consented and enrolled in the study will be randomized to either the MBSR Arm or the MBSR + PAP arm using a randomization plan generated by the SAS code, PROC plan. The study will be open label and participants will be informed as to study arm assignment prior to the first MBSR session. There will be rolling enrollment in trial participation up until the cut-off registration date prior to each MBSR course starting date. Each arm will be run independently given likely variation on numbers of participants willing to complete each study arm however efforts will be made to run both arms concurrently depending on recruitment. While the MBSR only arm can be completed on an individual basis for each participant the MBSR + PAP arm includes group-based psilocybin-assisted therapy interventions which requires 2-5 participants per MBSR cohort. We will leave open the option of running group PAP sessions for a cohort of only 2 participants however will have a goal participant number per cohort of 4 with the possibility of running up to 5 participants per cohort through this arm. To assess expectancy effects on treatment response participants will be administered expectancy scales prior to randomization to assess preference as well as post randomization to assess credibility.

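### The MBSR arm runs to 12 completers while enrolment is fixed at 12 per arm: the two rules agree only if no MBSR participant drops out, and the MBSR + PAP arm has no matching rule

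*Protocol*

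**What the plan says.** Section 4.1 (Description) gives two numbers for the MBSR arm. Eligible, consenting participants "will be randomized to either MBSR or MBSR + PAP with 12 participants per group". Later in the same paragraph, after the remarks on course capacity and outside providers, it says: "We will run subjects through the MBSR curriculum in flexible numbers concurrently until a total of 12 have completed this arm". The first counts people randomised, the second people who finish.

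Section 4.2 repeats the first count: "This study will enroll a total of 24 patients with 12 patients in each study arm". The Study Summary (Statistical Methodology) builds the feasibility criterion on it, asking for 24 to be enrolled and "for at least 16/24 patients to remain in the study until completion". Section 1.1 makes completion a primary feasibility measure: "Feasibility will be measured by the number of enrollees who successfully complete each modality in both study arms".

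For MBSR + PAP there is a number randomised but no target number of completers. The protocol states no replacement rule for either arm. Section 9.2 specifies a randomisation plan generated in advance and rolling enrolment, and adds: "Each arm will be run independently given likely variation on numbers of participants willing to complete each study arm". Section 12.1 makes the primary analysis intention-to-treat on everyone enrolled and randomised.

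The total is not settled elsewhere either. The Study Summary table has "Number of Subjects | 25", and Section 4.4 has the ambiguous "There will be a total of two groups of 12 subjects per study arm".

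**The concern.** A target counted in completers and a target counted in people randomised are different stopping points for accrual. Once one MBSR participant fails to finish, staff cannot satisfy both. If they follow the completer sentence, someone must be added to MBSR, and nothing equivalent happens in MBSR + PAP.

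Three things are at stake:

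- **Allocation.** The planned 12 against 12 no longer holds. The protocol does not say how an added participant would be allocated, so an extra MBSR entrant may not come from the randomisation list.
- **Comparability.** Topping up completers in one arm selects on a post-randomisation outcome in that arm only.
- **Feasibility.** The retention criterion has 24 as its denominator. With extra MBSR entrants, it is unclear whether the denominator stays at 24 or grows, and whether the replaced participants still count. Retention is something this pilot exists to measure.

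**Working it through.** **Inputs**

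- MBSR target: 12 completers (Section 4.1).
- Randomised: 12 per arm, 24 in total (Sections 4.1 and 4.2).
- Retention criterion: 16 of 24 (Study Summary).
- Completion rate: the protocol states none for this trial. The rate of 82% is one that Section 12.2 (Sample size determination) cites from a prior study. It is used here only as an illustration, with 90% and 70% as assumed values on either side.

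**The plan's own figures.** 12 + 12 = 24, and 16/24 = 66.7%. These agree with each other. The criterion tolerates 24 − 16 = 8 losses, so the plan does not itself expect zero attrition.

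**Step 1: will the two rules collide?** With 12 MBSR entrants and independent completion at rate *c*, the chance that fewer than 12 complete is 1 − *c*^12.

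**Step 2: how many entrants does the completer target need?** On average 12/*c*, rounded up. Adding 12 for MBSR + PAP gives the total.

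| Completion rate *c* | 1 − *c*^12 | 12/*c* | MBSR entrants | Total |
|---|---|---|---|---|
| 90% | 72% | 13.3 | 14 | 26 |
| 82% | 91% | 14.6 | 15 | 27 |
| 70% | 99% | 17.1 | 18 | 30 |

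At the criterion's own 66.7%, 12/0.667 = 18 entrants, again a total of 30. None of these totals is 24.

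**Step 3: what happens to the retention criterion?** This depends on a denominator that the protocol does not fix. Suppose, for illustration, that the 12 MBSR completers also all remain to the end of follow-up. Let *p* be true MBSR + PAP retention.

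- *Denominator kept at 24.* MBSR + PAP needs 16 − 12 = 4 of 12. P(Bin(12, *p*) ≥ 4) = 93% at *p* = 50% and 77% at *p* = 40%.
- *Denominator grows with enrolment (82% case, 27 enrolled).* The same two-thirds threshold is 18 of 27, so MBSR + PAP needs 18 − 12 = 6 of 12. P(Bin(12, *p*) ≥ 6) = 61% at *p* = 50% and 33% at *p* = 40%.
- *Reference: fixed 12 + 12, no replacement, MBSR retention 82%.* The 16 of 24 criterion is met with probability 57% at *p* = 50% and 35% at *p* = 40%.

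The criterion is materially easier only if extra MBSR entrants are admitted and the denominator nevertheless stays at 24. With a denominator that counts everyone, it behaves much as under fixed enrolment (61% against 57%, 33% against 35%).

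**The case against.** The strongest reply is that the sentence is a scheduling remark. It follows the discussion of course capacity and precedes the group format of the psilocybin sessions. Section 9.2 likewise says that the MBSR arm can be completed individually while the other arm needs cohorts. On this reading it means only that MBSR has no minimum group size and that all 12 assigned will be put through. The same paragraph has already fixed 12 per group, and the word *replace* appears nowhere. This reading is possible and may be what was meant. It does not remove the word *completed*, though, and no other section says what happens after an MBSR dropout.

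It can also be said that Section 12.1 keeps everyone randomised in the primary analysis, and that Section 1.1 looks at completion in both arms, so poor retention on psilocybin would be visible. Both points stand. Neither says whether MBSR dropouts are replaced, how a replacement is allocated, or what the retention denominator is.

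A reader might go further and infer that replacements would be late, non-concurrent entrants because the MBSR + PAP arm is already full. The protocol does not say which arm fills first. Section 9.2 plans rolling enrolment with efforts to run the arms concurrently, and the arm that needs cohorts could equally fill last.

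A reader might also infer that 12 retained MBSR participants are guaranteed, so that the criterion needs only 4 from the other arm. That equates finishing an 8-week curriculum with remaining in the study, whereas Section 4.4 follows participants for 180 days after the intervention. It also keeps 24 as the denominator after more than 24 have been enrolled, which no section states.

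**Conclusion.** The contradiction holds. A completer target in one arm and a fixed 12 randomised per arm are compatible only with zero MBSR attrition, and at the completion rates shown a collision is likely to very likely (72% to 99%). Followed literally, the completer sentence means about 2 to 6 extra MBSR entrants, a total of 26 to 30 instead of 24, topping-up in one arm only, and an undefined retention denominator.

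The sizes rest on assumed completion rates and independent dropout; the 82% is a prior-study figure, not a planning assumption of this trial. The effect on the feasibility criterion is conditional: it could be made easier to pass, but only under one handling of the denominator and only if MBSR completers also stay through the 6-month follow-up. The documents do not support a claim that the criterion is void or that the comparator will be non-concurrent. This is a wording conflict worth settling before accrual, because entrants added outside the randomisation list cannot be undone afterwards.

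**What to change.** 1. In Section 4.1, replace the completer sentence with wording such as: *The 12 participants randomised to MBSR will attend the curriculum in groups of flexible size.* This keeps the scheduling message and drops the completer target.
2. State in Section 4.2 that non-completers are not replaced in either arm. If replacement is wanted, give one rule for both arms and apply it through the randomisation list.
3. Define the retention denominator as all randomised participants, and report retention by arm as well as pooled.
4. Bring the subject number in the Study Summary table and the group-size wording in Section 4.4 into line with Section 4.2.

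The cost is a few sentences. With no replacement, the number of MBSR completers may fall below 12.

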### MBSR+PAP Arm

Participants randomized to the MBSR + PAP arm will participate in the same curriculum as described above, however, will substitute a group PAP session instead of the group MBSR retreat. The PAP intervention will be facilitated with a 1:1 therapist/participant ratio with an additional lead therapist. Group size will be determined by ease of recruitment but will be no fewer than 2, and no more than 6 participants per PAP session. The group will be overseen by a lead therapist who will be available through the entirety of the dosing session and will not be assigned to any one individual participant. Timing of the PAP session will be during the MBSR curriculum with a goal of scheduling at same time as the MBSR retreat for the other arm. However, scheduling will be flexible depending on participant schedules, particularly given working demands of healthcare providers amid a pandemic: this session may occur before or after the group meditation retreat +/- 1 week. The psilocybin session will be accompanied by 3 preceding group preparatory sessions of 90 minutes each (one of these can be via Zoom per participant) as well as 3 integration sessions of 90 minutes each (up to two of these can be via Zoom per participant). Participants must continue to meet all inclusion criteria as well as hepatic and renal function requirements laid out in inclusion and exclusion criteria to receive psilocybin.

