## Stopping Rules

For 14 days following psilocybin administration, subjects will be monitored for adverse events. Study will be placed on hold and the study will be reevaluated if there is an occurrence of any grade 3 (or above) adverse event attributed to psilocybin in the first cohort of participants. These include hypertensive emergency or other serious cardiac events and other need for hospitalization attributed to psilocybin administration. For 28 days following psilocybin administration, subjects will be monitored for acute suicide ideation and suicide attempt. Any suicide attempt throughout the trial will also preclude further enrollment. Any attempt whether completed or not will be recognized as a serious adverse event and warrant study closure. Subjects’ physical and psychiatric states will be closely followed throughout the trial and for 28 days after psilocybin administration. If neither stopping rule is met, then the study will open for continuation. There will be no further administrations of study drug within this 28 day window. If the stopping rule is reached prior to the end of enrollment, the analyses will still be performed for those patients who have completed treatment prior to the time the stopping criterion is reached. In this case, the statistical power for the analyses may be reduced.

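### The safety pause after four patients (4.1) relies on a grade 3+ stopping rule that 11.3 limits to the first cohort, which may be only two or three people

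*Protocol*

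**What the plan says.** **The pause.** Section 4.1 of the protocol says: "After the enrollment and treatment of the first four patients, accrual will be placed on hold to ensure participant safety". It continues: "If stopping rules are not met, we will continue with enrollment". It does not say which arm the four patients belong to.

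**The rules that decide it.** Section 11.3 puts the study on hold for "any grade 3 (or above) adverse event attributed to psilocybin in the first cohort of participants". Its other rule has a wider scope: "Any suicide attempt throughout the trial will also preclude further enrollment". The section lets the study continue if neither rule is met. It also states: "There will be no further administrations of study drug within this 28 day window". Section 15.5 repeats this 28-day bar.

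**The size of a cohort.** Section 4.1 says: "The psilocybin intervention will be completed in groups of 2-6 individuals per cohort". Section 6.1 says: "Group size will be determined by ease of recruitment but will be no fewer than 2, and no more than 6 participants per PAP session". Section 9.2 gives a range of 2 to 5 with a goal of 4, and adds: "We will leave open the option of running group PAP sessions for a cohort of only 2 participants".

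**The concern.** The pause is counted in patients (four), but the grade 3+ rule that decides it is counted in cohorts (the first one). In these sections a cohort is a treatment group whose size depends on recruitment. The two units match only if the first psilocybin group has exactly four people, which 9.2 sets as a goal and not as a requirement.

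If the first group is smaller, part of the four-patient review set lies outside the grade 3+ rule. The check could then be passed, as worded, although one of the four had a severe drug-attributed event. The cohort limit applies to this rule alone, since the suicide-attempt rule in the same section covers the whole trial.

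**Working it through.** The protocol states no operating characteristic for the pause, so there is no figure to reproduce. The check is a comparison of the sections, followed by a calculation for scale.

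**Step 1: compare the units.** Read the four patients in 4.1 as psilocybin-dosed.

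| First group | Of the first four dosed, covered by the grade 3+ rule | Not covered |
|---|---|---|
| 2 | 2 | 2 (third and fourth) |
| 3 | 3 | 1 (fourth) |
| 4 | 4 | 0 |
| 5 or 6 | 4 | 0 |

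With 5 or 6, everyone is dosed in one session, so the pause cannot fall after exactly four. The rule covers the whole group, so this does no harm.

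**Step 2: scale.** Inputs are the first-group size k = 2 or 3 (4.1, 6.1, 9.2), the four patients of 4.1, and a per-participant grade 3+ rate p. The protocol gives no such rate, so p = 1%, 5%, 10% and 20% are assumptions. Events are taken as independent between participants.

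- Chance that a rule covering n people is triggered: 1 − (1 − p)^n.
- Chance of an event among the first four that the rule misses (none in the first group, at least one in the rest): (1 − p)^k × [1 − (1 − p)^(4 − k)].

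Example with p = 10% and k = 2: 0.9² = 0.81, 1 − 0.81 = 0.19, and 0.81 × 0.19 = 0.154.

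| p | Triggered, first group 2 | Triggered, first group 3 | Triggered if all four covered | Missed, first group 2 | Missed, first group 3 |
|---|---|---|---|---|---|
| 1% | 2.0% | 3.0% | 3.9% | 2.0% | 1.0% |
| 5% | 9.8% | 14.3% | 18.5% | 8.8% | 4.3% |
| 10% | 19.0% | 27.1% | 34.4% | 15.4% | 7.3% |
| 20% | 36.0% | 48.8% | 59.0% | 23.0% | 10.2% |

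For a first group of four or more, the missed chance is 0. All these figures are conditional on the first group size, and the protocol gives no basis for the chance that the first group falls short of four.

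**Step 3: what still applies to an event that the rule misses.** The suicide-attempt rule covers all participants. Section 15.3 requires that the IRB and DSMB be told of every serious adverse event, has the full DSMB review serious events monthly, and stops the study if the DSMB or investigator is concerned about unexpected safety issues. Other events reach the DSMB at its quarterly review. Section 15.3 also withdraws a participant who has a serious or unexpected event, but that does not hold the study. None of these is an automatic hold triggered by a grade 3 event.

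**The case against.** **One intended unit.** The sponsor may have meant the first cohort to be the four patients under review. The goal in 9.2 is also four, and 4.1 and 11.3 both end with the study continuing if no rule is met. This is plausible as intent. But no section defines the first cohort that way, and 9.2 expressly keeps a group of two open. A stopping rule is applied as written.

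**The arm is not named.** If the four are counted across both arms, a first group of two could contain every dosed person among them, and nobody in the review set would be left out. This stands, and the point is conditional on it. On that reading, though, the pause may rest on fewer than four exposures, so 4.1 needs the same clarification.

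**Other safeguards.** The events that 11.3 gives as examples would largely be serious adverse events and so reach the DSMB. This also stands. A reader might infer that a severe event in the third or fourth dosed participant would go unnoticed or could not stop the trial. The protocol does not support that; only the automatic trigger is lost.

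**Dosing during the pause.** Because 4.1 mentions only accrual, a reader might infer that people already enrolled would still be dosed during the hold. The protocol does not support that either. Section 11.3 bars further administrations for 28 days. Each participant receives one dose, so the bar has an effect only if it is study-wide. What is left open is whether it repeats after later groups.

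**The rates.** Section 7.1 reports no serious adverse events in over 2000 doses. Serious and grade 3 are different scales, but nothing in the protocol supports 10% or 20%. The table shows scale and is not a forecast.

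**Conclusion.** The point holds in a limited form. As worded, a grade 3+ psilocybin-attributed event in the third or fourth dosed participant can fall outside the rule that decides the four-patient pause. Two conditions are needed: a first psilocybin group of two or three, which the protocol allows, and a reading of the four patients as psilocybin-dosed, which 4.1 does not state. With a first group of four or more there is no gap.

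Under those conditions and an assumed rate of 1% to 20%, the chance of a missed event among the first four is about 2% to 23% with a first group of two, and 1% to 10% with three. No efficacy analysis is affected. The wording should be corrected because the stated rule gives a weaker check than 4.1 presents, and aligning the units is easy.

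**What to change.** - **Section 4.1:** say that the pause follows treatment of the first four psilocybin-dosed participants, and that accrual and dosing are both held for 28 days after the session in which the fourth is dosed.
- **Section 11.3:** in place of the limit to the first cohort, apply the grade 3+ rule to all participants dosed up to and including the session in which the fourth participant is dosed. That is one session if the first group is four or more, and two if it is two or three.
- **Sections 11.3 and 15.5 (minor):** state that the 28-day bar is study-wide, and whether it repeats after later groups.

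The change cannot deadlock. The pause in 4.1 does not hold accrual before the fourth participant is dosed, and two groups of at least two always reach four.

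**Cost.** This is protocol wording. With a first group of four to six nothing is added, because the accrual hold and the 28-day bar are already there. With a first group of two or three, the hold after the second session delays the next dosing by at most 28 days, and by nothing if the bar already applies after every group. Session dates need planning around the hold, because 6.1 allows only one week either side of the retreat. A grade 3+ event in the third or fourth dosed participant would now pause the study.
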